## Abstract

**Background:**

Bowel cancer is common and a major cause of death. The NHS is currently rolling out a national bowel cancer screening programme that aims to cover the entire population by 2010. The programme will be based on the Faecal Occult Blood test (FOBt) that reduces mortality from colon cancer by 16%. However, FOB testing has a relatively low positive predictive value, with associated unnecessary cost, risk and anxiety from subsequent investigation, and is unacceptable to a proportion of the target population. Increased levels of an enzyme called matrix metalloproteinase 9 (MMP9) have been found to be associated with colorectal cancer, and this can be measured from a blood sample. MMP9 has potential for detecting those at risk of having colorectal cancer. The aim of this study is to assess whether MMP9 estimation enhances the predictive value of a positive FOBt.

**Methods and design:**

FOBt positive people aged 60–69 years attending the Wolverhampton NHS Bowel Cancer Screening Unit and providing consent for colonoscopy will be recruited. Participants will provide a blood sample prior to colonoscopy and permission for collection of the clinical outcome from screening unit records. Multivariate logistic regression analyses will determine the independent factors (patient and disease related, MMP9) associated with the prediction of neoplasia.

**Discussion:**

Colorectal cancer is a major cause of morbidity and mortality. Pilot studies have confirmed the feasibility of the national cancer screening programme that is based on FOBt. However, the test has high false positive rates. MMP9 has significant potential as a marker for both adenomas and cancers. This study is to examine whether using MMP9 as an adjunct to FOBt improves the accuracy of screening and reduces the number of false positive tests that cause anxiety and require invasive and potentially harmful investigation.

## Background

About one in 20 people in the UK will develop colorectal cancer during their lifetime [1]. It is the third most common cancer in the UK, and the second leading cause of cancer death, with over 15,000 people dying from colorectal cancer each year [2]. Colorectal cancer incurs an annual expenditure of more than £300 million in surgical, adjuvant, and palliative treatment [3]. As the population ages these costs are set to increase. Reduced costs of treatment could be achieved by earlier diagnosis. However, most cases are diagnosed at a late stage which is strongly associated with poorer survival; the five year overall survival rate of colorectal cancer is only 48% [4]. Benefits, in terms of improved survival, improved quality of life and reduced treatment costs, could be accrued by earlier diagnosis.

FOBt screening can detect colorectal cancer at an early stage when treatment is more likely to be effective. It also provides an opportunity to identify precursors to invasive disease, polyps, which can be removed during colonoscopy and reduce the risk of colorectal cancer developing. Randomised controlled trials suggest that colorectal screening has the potential to reduce colorectal cancer mortality by 16% [5]. In the light of the evidence from these trials the NHS has introduced a national bowel cancer screening programme [6]. The first UK bowel cancer screening site started screening men and women aged 60–69 years in July 2006 and national coverage is expected to be achieved by 2010. The programme uses the Faecal Occult Blood test (FOBt). Participants in screening, who have a positive FOBt, are then invited for colonoscopy. Pilot evaluations, in Scotland and Rugby, confirmed the feasibility of the national screening programme; however, they also demonstrated relatively low acceptability of FOBt with uptake rates of only 58.5%[7] and 52% [8] in the first and second rounds of screening respectively.

Recent results from the NHS Bowel Cancer screening pilot studies demonstrate that, FOBt testing has a sensitivity of 57.7%, with a positive predictive value of 5.3% for cancer and 38.8% for neoplasia [8]. The low positive predictive value means that although all FOBt positive results require investigation via colonoscopy, many of these are false positive results with the associated cost, risk and anxiety. Colonoscopy carries a risk of bowel perforation of 1 in 1,500 [9].

Therefore, although FOBt screening is likely to reduce the mortality attributable to bowel cancer there is an urgent need to improve the screening test, ideally to increase the positive predictive value. Serum matrix metalloproteinase 9 (MMP9) are proteolytic enzymes that are associated with tissue remodelling in normal and pathological processes [10]. Over-expression of MMP9s has been correlated with progression in many tumour types, including colorectal cancer [11-13]. Our pilot suggests that MMP9 has potential in detecting those at risk of having colorectal cancer as it demonstrates a high specificity and positive predictive value [11].

### Pilot work

A pilot study of 300 patients attending the Queen Elizabeth Hospital colorectal clinic was performed. Twenty seven significant adenomas and 63 malignancies were identified in the study population. Patients had a standard assessment, by proforma-led history and examination, with rigid sigmoidoscopy to the recto-sigmoid junction. The patients gave serum samples for analysis, and referral for specialist investigations occurred as per the clinic-protocol. Forty-six "normal" volunteers also donated serum. ELISAs were done on each serum sample, and the results were compared with the clinical diagnosis. The median sMMP9 concentration was 443 ngml^-1^. The model accurately predicted neoplasia in 77.3% of cases (sensitivity 77.9%, specificity 77.1%, positive predictive value (PPV) 44.6%, and negative predictive value (NPV) 95.8%) in a population with 30% prevalence of disease [11].

The results of this pilot suggest that MMP9 may be an effective secondary screening test, but this study was completed in a selected population. The performance of a diagnostic test can vary in populations with different severity and prevalence of disease and, therefore, the acceptability and accuracy of MMP9 needs to be established in the target population [14].

### Study aim

The aim of the study is to assess whether the addition of MMP9 testing enhances the predictive value of a positive FOBt.

## Methods

Study design: evaluation of a diagnostic test.

Setting: Wolverhampton NHS Bowel Screening Unit

Subjects: Participants in the NHS Bowel Cancer Screening Programme who are FOBt positive and attending for colonoscopy.

Those consenting to colonoscopy will be given a patient information leaflet about the study. Prior to colonoscopy, all those expressing an interest, will be seen by a member of the research team who will answer any outstanding questions and seek consent.

Intervention: Participation will entail the provision of a blood sample prior to colonoscopy, completion of a baseline questionnaire (demographics, symptoms, and duration of symptoms) and permission for data collection (final diagnosis) from screening unit records.

A trained nurse/phlebotomist will take two blood samples (10 ml) to enable MMP9 determination and for a routine haematology profile: Haemoglobin (Hb), Whole blood cell count (WBC) and Red cell count (RCC). Blood samples will be kept on ice and spun within 4 hours of collection. Local storage will be at -80C until transported to the Department of Cancer Studies, University of Birmingham, for analysis.

Outcomes assessment: diagnosis collected from screening office records. A technician, blinded to the symptoms, signs, or diagnosis of the patient, will determine MMP9 levels by ELISA. Duplicate determinations will be performed upon coded samples.

### Procedures for handling data

All electronic data will be processed using password protected systems and paper data will be stored securely in locked cabinets/rooms. Participant identification numbers will be employed to enable separate storage/processing of name and address data. Identifiable data will be handled only by University of Birmingham staff working on this study who are trained in policies and procedures related to confidentiality.

### Sample size estimation

In a 12 month period, 200 people are expected to have a positive FOBt as part of the screening programme and be referred to Wolverhampton Screening Centre.

Our pilot data indicates that elevated MMP9 has a high sensitivity and negative predictive value. The potential of measuring MMP9 in FOBt positive people will be to reduce the number of unnecessary colonoscopies i.e. a high NPV is required. The pilot data indicated that 126 test negative patients are needed to detect a NPV of 95% with 5% precision and 2-sided alpha of 1%. Based on this data, a total of 209 patients are required to enable 91% and of 31% prevalence.

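### The study is sized on the NPV of a test-negative result, but the planned analysis refits a model and applies no pilot rule whose NPV could be estimated

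*Protocol article*

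**What the plan says.** All references are to the protocol article.

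- **Background** (paragraph introducing MMP9): the pilot is said to support the marker "as it demonstrates a high specificity and positive predictive value".
- **Pilot work**: "The model accurately predicted neoplasia in 77.3% of cases". Sensitivity is 77.9%, specificity 77.1%, PPV 44.6% and NPV 95.8%, "in a population with 30% prevalence of disease". These are the only pilot accuracy figures in the article. The contents of the model are not described.
- **Sample size estimation**: "Our pilot data indicates that elevated MMP9 has a high sensitivity and negative predictive value". The section argues that a high NPV is what would spare people colonoscopy. It then says that "126 test negative patients are needed to detect a NPV of 95% with 5% precision and 2-sided alpha of 1" per cent, and that "a total of 209 patients are required to enable 91% and of 31% prevalence". The last sentence has plainly lost words: the 91% has no label.
- **Analyses**: a logistic model for high-risk disease is derived in this cohort without MMP9, then MMP9 is added. The two models are compared on sensitivity, specificity, proportions of false positives and negatives, percentage correct, and AUC. NPV is not on the list, and no rule from the pilot is applied.

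**The concern.** A sample size based on the precision of an NPV needs a test that already says who is negative. Three sections describe the pilot evidence for that test differently: a model (Pilot work), a raised MMP9 with good sensitivity and NPV (Sample size estimation), and MMP9 with good specificity and PPV (Background). The Analyses section then uses none of these as a fixed rule.

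Two things are at stake. First, the study could finish without an estimate of the quantity it was sized for, or with one for a classification that did not exist when the size was set. Second, a model judged in the patients used to fit it tends to look better than it would in new patients. That matters when the proposed use is to let people with a positive FOBt avoid colonoscopy.

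**Working it through.** **1. The 126.** Inputs from Sample size estimation: NPV 0.95, precision 0.05, two-sided alpha 1% (z = 2.576).

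n = z² × p(1 − p) / d² = 2.576² × 0.95 × 0.05 / 0.05² = 126.06.

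The 126 reproduces. It is the number of test negatives that gives a 99% confidence interval of ±5 points around an NPV of 95%, whatever the test is.

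**2. The 209.** The total is 126 divided by the share testing negative: N = 126 / [prev × (1 − sens) + (1 − prev) × spec]. The printed numbers imply a share of 126/209 = 60.3%. At the stated 31% prevalence:

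| Sensitivity | Specificity | Share negative | N | NPV |
|---|---|---|---|---|
| 77.9% (pilot model) | 77.1% (pilot model) | 0.31 × 0.221 + 0.69 × 0.771 = 60.05% | 209.8 | 0.532/0.6005 = 88.6% |
| 91% (unlabelled figure) | 83% (not printed) | 0.31 × 0.09 + 0.69 × 0.83 = 60.06% | 209.8 | 0.5727/0.6006 = 95.4% |
| 91% | 77.1% | 55.99% | 225 | 95.0% |
| 77.9% | 91% | 69.64% | 181 | 90.2% |

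The first two rows both fit. In whole counts the second is neater. Take 209 patients, 65 cases and 126 negatives, of whom 6 are false and 120 true. Then prevalence is 65/209 = 31%, sensitivity 59/65 = 91%, NPV 120/126 = 95% and specificity 120/144 = 83%. That accounts for every figure in the sentence, but its 83% appears nowhere in the article. The first row uses printed figures only, but leaves the 91% unexplained and gives the wrong NPV.

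**3. What follows if the test is the pilot model.** With NPV 88.6% and 126 negatives, the 99% half-width is 2.576 × √(0.886 × 0.114 / 126) = 7.3 points. Holding ±5 points would need 2.576² × 0.886 × 0.114 / 0.05² ≈ 268.2, so 269 negatives, and 268.2/0.6005 ≈ 447 patients. If the second row applies, the stated precision stands.

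**4. What follows if the test is an MMP9 cut-off.** Neither its accuracy nor its share of negatives is given. Over assumed shares negative of 50%, 60% and 70%, N = 126/share = 252, 210 and 180.

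**5. Sizing against analysis.**

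| | Sample size estimation | Analyses |
|---|---|---|
| Test | raised MMP9, from the pilot | new logistic model with MMP9 added |
| Source of the rule | earlier data | this cohort |
| Quantity | NPV among test negatives | sensitivity, specificity, error proportions, percentage correct, AUC |
| Assessed in | target population | the same patients used for fitting |

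**The case against.** The strongest reply has five parts.

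- **The pilot model may itself be MMP9 alone.** Its predictors are not listed, and Pilot work concludes in favour of MMP9 as a secondary test. This stands: a reader might infer that the model's accuracy was wrongly credited to the marker. That is likely but not proven.
- **The 209 need not come from the model.** This also stands. A reader might infer that only the model's figures produce 209, but the second row of the first table shows otherwise.
- **The aim is added value.** Study aim asks whether adding MMP9 helps, and Pilot work asks for the accuracy of MMP9, not of an equation, to be established in the target population. Comparing models with and without MMP9 serves that aim. This stands, and it rules out replacing the planned comparison with the pilot model.
- **A cut-off, or a correction for optimism, may sit in the full protocol or SAP.** Agreed: a missing threshold is not the finding here. A reader might take the pilot median of 443 ng/ml as the threshold, but the article never calls it one.
- **The proportion of false negatives could be 1 − NPV.** It could, if its denominator is the test negatives, which is not stated. Even so, it would describe the refitted models, not the rule behind the sample size.

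The difference between Background and Sample size estimation is one of emphasis. Sensitivity and specificity are nearly equal at 77.9% and 77.1%, so the two sections do not contradict each other on fact, though they cite different strengths of one pilot.

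**Conclusion.** The point holds as a mismatch between sizing and analysis. The study is sized to estimate the NPV of a test-negative result. The analysis described builds a new model in the same cohort, assesses it there, names no NPV and applies no rule fixed beforehand. The 126 is correct. The 209 is arithmetically plausible, but its origin is open.

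The size depends on which rule was meant. If it is the pilot model at its printed sensitivity and specificity, the expected NPV at 31% prevalence is about 88.6% and the 99% half-width 7.3 points, against the planned 95% and 5 points. If it is a rule with about 91% sensitivity and 83% specificity, the planned precision is met. These figures are conditional, and the pilot summary is not firm ground: at its stated 30% prevalence, its sensitivity and specificity give NPV 0.5397/0.606 = 89.1% and PPV 0.2337/0.394 = 59.3%, against the printed 95.8% and 44.6%.

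The optimism of the refitted model cannot be sized from the article. A reader might also infer that MMP9 alone must perform worse than the pilot model. No accuracy for MMP9 alone is given, so any such figure would rest on assumption.

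**What to change.** - In Sample size estimation, state which pilot rule defines a negative test (the pilot model or an MMP9 cut-off), and restore the missing words so that the 91% is labelled and the 209 can be traced.
- Word Background, Pilot work and Sample size estimation consistently about what the pilot evaluated and what it showed.
- Keep the comparison of models with and without MMP9 for the stated aim.
- Add one prespecified analysis that applies the named pilot rule unchanged to this cohort and reports its NPV with a 99% confidence interval, and its PPV.
- If the pilot rule needs predictors not collected here, use the pilot's MMP9 cut-off instead and restate the expected number of test negatives.

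The cost is wording and one extra analysis, with no further procedures; the added analysis needs no more patients. It assumes that the pilot rule can be retrieved, which is reasonable because the article presents the pilot as the team's own. The downside is that a fixed rule will probably look less accurate than a refitted model.

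### The planned 95% NPV with 5-point precision does not follow from the pilot accuracy and prevalence that appear to underlie the sample size, and the different lesion mix may lower it further

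*Protocol article*

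**What the plan says.** The Sample size estimation section of the protocol article rests its planning on the pilot: "Our pilot data indicates that elevated MMP9 has a high sensitivity and negative predictive value". It then says: "The pilot data indicated that 126 test negative patients are needed to detect a NPV of 95% with 5% precision", with a two-sided alpha of 1%. The total follows in a sentence that has lost words: "a total of 209 patients are required to enable 91% and of 31% prevalence". What the 91% refers to is not stated, and the section does not say which sensitivity and specificity were used.

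The Pilot work section describes 300 colorectal clinic patients: "Twenty seven significant adenomas and 63 malignancies were identified in the study population". It reports one pooled sensitivity (77.9%) and specificity (77.1%), a PPV of 44.6% and an NPV of 95.8%, at 30% prevalence. It gives no split by cancer and adenoma. The same section cautions that this was a selected population and that test performance depends on severity and prevalence.

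For the population to be studied, the Background gives the FOBt result "with a positive predictive value of 5.3% for cancer and 38.8% for neoplasia". The Analyses section defines the target condition as invasive adenocarcinoma or high risk polyps.

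**The concern.** The sample size section moves a predictive value from one population to another with no adjustment, although the Pilot work section explains why that is unsafe. Two separate things are involved.

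- NPV depends on prevalence, sensitivity and specificity together. A planned NPV should therefore agree with the sensitivity, specificity and prevalence used to turn test negatives into a total number of patients.
- Pooled sensitivity depends on the mix of lesions. The pilot mix was mostly cancers; most lesions in FOBt-positive screenees will be polyps. The Background remarks: "Over-expression of MMP9s has been correlated with progression in many tumour types, including colorectal cancer". That makes lower sensitivity for polyps plausible, though it does not establish it.

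The section itself presents a high NPV as the property that would let a negative MMP9 result spare a colonoscopy. If the expected NPV and its precision are overstated, readers will have the wrong idea of what 209 patients can show on that quantity.

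**Working it through.** **Inputs.** Planned NPV 95%, half-width 5 points, two-sided alpha 1% (z = 2.576), 126 test negatives, 209 patients, prevalence 31%: Sample size estimation. Pilot sensitivity 77.9%, specificity 77.1%, 63 cancers and 27 adenomas: Pilot work. Yield of 5.3% cancer and 38.8% neoplasia: Background.

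**1. The plan's own figures.**

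Test negatives: n = z² × NPV × (1 − NPV) / 0.05² = 2.576² × 0.95 × 0.05 / 0.0025 = 126. This matches.

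Proportion test negative, with pilot accuracy at 31% prevalence: 0.31 × (1 − 0.779) + 0.69 × 0.771 = 0.0685 + 0.5320 = 0.6005. Total: 126 / 0.6005 = 209.8, against the stated 209. The match is close, but the link is inferred.

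**2. The NPV those inputs imply, before any case-mix shift.**

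NPV = 0.5320 / 0.6005 = 88.6%.

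Test negatives among 209: 209 × 0.6005 = 125.5. The 99% half-width is 2.576 × √(0.886 × 0.114 / 125.5) = 7.3 points.

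The gap to 95% may already lie in the pilot's reported figures: at 30% prevalence, 77.9% and 77.1% give an NPV of 0.5397 / 0.6060 = 89.1%, not 95.8%. With specificity 77.1% and 31% prevalence, an NPV of 95% needs a sensitivity of about 91%.

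**3. Lesion mix.**

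Cancer share in the pilot: 63/90 = 70%. In FOBt-positive people: 5.3/38.8 = 13.7%, or 5.3/31 = 17.1% at the planned prevalence. If some neoplasia is not high risk, the target condition is rarer than 38.8% and the cancer share rises.

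**4. Effect of case mix, by assumption.** Sensitivity by lesion type is not given. Let Sc be an assumed sensitivity for cancers, and choose Sa for adenomas so that the pilot mix pools to 77.9%: Sa = (0.779 − 0.70 × Sc) / 0.30. Re-weight: S = 0.171 × Sc + 0.829 × Sa. Then NPV = 0.5320 / (0.5320 + 0.31 × (1 − S)), and the half-width uses 209 × P(test negative).

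| Sc | Sa | S | Test negatives of 209 | NPV | 99% half-width (points) |
|---|---|---|---|---|---|
| 77.9% | 77.9% | 77.9% | 125.5 | 88.6% | 7.3 |
| 80% | 73% | 74% | 128 | 87% | 7.7 |
| 85% | 61% | 65% | 134 | 83% | 8.3 |

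The first row is the baseline of step 2. From there to the third row, case mix costs 88.6 − 83.2 = 5.4 points of NPV and about 1 point of half-width.

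**5. If the pooled sensitivity were 91%.** With specificity 77.1% and no case-mix shift, NPV is 95.0%, with 117 test negatives and a half-width of 5.2 points. With the same 70/30 weights and Sc of 95% to 100% (Sa 82% to 70%), NPV is 91% to 87% and the half-width 6.5 to 7.6 points.

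**The case against.** **The inputs are inferred.** The sentence giving 209 is incomplete. The section's own numbers allow another reading: 126 negatives at an NPV of 95% contain 6.3 false negatives; 31% of 209 is 64.8 cases; sensitivity is then 1 − 6.3/64.8 = 90%, near the unexplained 91%. Specificity would be 119.7/144.2 = 83%, which the article states nowhere. On that reading there is no baseline shortfall. Neither reading can be proved. This stands, and is a reason to have the inputs stated. The only pilot sensitivity and specificity in the document remain 77.9% and 77.1%.

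**The case-mix loss is assumed.** No section gives sensitivity by lesion type, and the Discussion describes MMP9 as a potential marker for both adenomas and cancers. A reader might infer that the lesion mix by itself defeats the planned NPV. The documents do not support that: equal sensitivities give no loss, and the drop from 95% to 88.6% arises without any case-mix shift.

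**The 70% weight is unconfirmed.** A sensitivity of 77.9% is not a possible proportion of 90 cases (70/90 = 77.8%, 71/90 = 78.9%), so it may not come from all 63 cancers and 27 adenomas. This stands, and limits the scenarios in steps 4 and 5 but not the baseline.

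**The NPV is not a success criterion.** A reader might infer that the study would fail if NPV came in under 95%. No section says so, and the Analyses section compares models by other accuracy measures and AUC. The defect lies in the stated planning value and precision.

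**Measuring accuracy in the target population is the study's purpose.** That justifies running the study. It does not justify taking its precision from unadjusted pilot values.

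**Conclusion.** The point holds as a defect in the stated planning values. The figure of 126 is correct arithmetic for an NPV of 95%; the planning NPV is what lacks support. On the only pilot sensitivity and specificity reported, at the planned 31% prevalence, 209 patients would be expected to show an NPV of 88.6% with a 99% half-width of about 7.3 points. This rests on the inference that those inputs were used. They would give an NPV of 95% only at a prevalence of about 15.5% or lower, which contradicts the stated 31%.

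The change in lesion mix is an additional risk in the same direction if adenomas are harder to detect than cancers. Its size is unknown: none with equal sensitivities, and about 1.7 or 5.4 further points of NPV in the two unequal scenarios shown, both of which depend on the unconfirmed 70/30 weighting.

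**What to change.** In the Sample size estimation section:

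1. State the sensitivity, specificity and prevalence used, and complete the sentence containing the 91%.
2. For the 209 patients, restate the expected NPV, number of test negatives and 99% half-width, starting from the unadjusted baseline.
3. Add a range re-weighted to the lesion mix expected in FOBt-positive people, using the pilot's sensitivity tabulated separately for cancers and adenomas and the definition of high risk disease in the Analyses section.
4. Drop the statement that the pilot supports a 95% NPV with 5% precision in this population.

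The cost is a re-tabulation of the pilot data and a rewritten paragraph. Recruitment does not change. The drawback is a less favourable stated NPV and precision.

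### The pilot accuracy figures contradict one another, and on either reading of them the pilot does not support the planned NPV of 95% with 5% precision at 1% alpha

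*Protocol article*

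**What the plan says.** The Pilot work section of the protocol article describes the pilot's size and yield: "A pilot study of 300 patients attending the Queen Elizabeth Hospital colorectal clinic was performed", and "Twenty seven significant adenomas and 63 malignancies were identified in the study population". That is 27 + 63 = 90 of 300, or 30%. It reports overall accuracy of 77.3% with "sensitivity 77.9%, specificity 77.1%, positive predictive value (PPV) 44.6%, and negative predictive value (NPV) 95.8%) in a population with 30% prevalence of disease".

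The Sample size estimation section makes NPV the design quantity, because the purpose is to "reduce the number of unnecessary colonoscopies i.e. a high NPV is required". Citing the pilot, it states that "126 test negative patients are needed to detect a NPV of 95% with 5% precision and 2-sided alpha of 1" per cent. It then gives the total: "a total of 209 patients are required to enable 91% and of 31% prevalence". The 91% has no label, and the sentence is incomplete as printed.

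**The concern.** Sensitivity, specificity and prevalence together fix PPV and NPV. The pilot paragraph prints all five, and they can be tested against each other. If the printed NPV does not follow from the other figures, a planning value of 95% taken from the pilot loses its support.

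Two things are at stake. A reader will expect about 1 in 20 MMP9-negative patients to have high-risk disease, and that rate is the argument for sparing such patients colonoscopy. The precision of a proportion also depends on its value: an NPV further below 95% has a wider interval for the same 126 test negatives.

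**Working it through.** Inputs from Pilot work: sensitivity (Se) 0.779, specificity (Sp) 0.771, PPV 0.446, NPV 0.958, accuracy 0.773, prevalence 0.30. Inputs from Sample size estimation: NPV 0.95, half-width 0.05, two-sided alpha 0.01, 126 test negatives, total 209, prevalence 0.31. The article names no interval method. The normal approximation is assumed because it reproduces the 126.

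1. **The plan's 126.** n = z² × NPV × (1 − NPV) / d² = 2.576² × 0.95 × 0.05 / 0.05² = 126.06. This matches.

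2. **The pilot figures at 30% prevalence.**
   - PPV = 0.30 × 0.779 / (0.30 × 0.779 + 0.70 × 0.229) = 0.2337 / 0.3940 = 59.3%, against 44.6% printed.
   - NPV = 0.70 × 0.771 / (0.70 × 0.771 + 0.30 × 0.221) = 0.5397 / 0.6060 = 89.1%, against 95.8% printed. Rounding of the inputs moves this only between 88.8% and 89.3%.
   - With this Se and Sp, the printed PPV needs a prevalence of about 19.1% and the printed NPV about 13.3%, so no single prevalence gives both.
   - Other denominators do not rescue the NPV. Adding the 46 volunteers (90/346) gives 90.8%, cancers only (63/300) gives 92.9%, and 63/346 gives 94.0%.
   - Accuracy does not settle the matter. At 30% it is 0.30 × 0.779 + 0.70 × 0.771 = 77.3%, as printed, but Se and Sp are so close that it hardly changes with prevalence.

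3. **Reading A: the printed Se and Sp are right.** At 31% prevalence:
   - Test-negative fraction = 0.69 × 0.771 + 0.31 × 0.221 = 0.5320 + 0.0685 = 0.6005.
   - NPV = 0.5320 / 0.6005 = 88.6%, so missed disease among test negatives is 11.4%.
   - Half-width with 126 test negatives, from √(0.886 × 0.114 / 126) = 0.0283: ±7.3 points at 99% and ±5.6 at 95%.

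4. **Reading B: the printed PPV, NPV and accuracy are right.** Let t be the test-positive fraction. Accuracy = PPV × t + NPV × (1 − t).
   - t = (0.958 − 0.773) / (0.958 − 0.446) = 0.185 / 0.512 = 0.361.
   - True positives = 0.446 × 0.3613 = 0.1612; false negatives = 0.042 × 0.6387 = 0.0268; true negatives = 0.6118.
   - Prevalence = 0.1612 + 0.0268 = 18.8%; Se = 0.1612 / 0.1880 = 85.7%; Sp = 0.6118 / 0.8120 = 75.3%.
   - At 31% prevalence, NPV = 0.69 × 0.753 / (0.69 × 0.753 + 0.31 × 0.143) = 0.5196 / 0.5639 = 92.1%, so missed disease is about 8%.
   - Half-width with 126 test negatives, from √(0.921 × 0.079 / 126) = 0.0240: ±6.2 points at 99% and ±4.7 at 95%.

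5. **What an NPV of 95% would need.** At 31% prevalence and Sp 77.1%, Se = 1 − (0.69 × 0.771 × 0.05 / 0.95) / 0.31 = 91.0%, against the pilot's 77.9%.

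6. **The total of 209.** With the pilot Se and Sp, 126 / 0.6005 = 209.8. With Se 91% and Sp 83%, the test-negative fraction is 0.69 × 0.83 + 0.31 × 0.09 = 0.6006. The total is again 209.8, and the NPV is 0.5727 / 0.6006 = 95.4%. The total therefore does not show which inputs were used.

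**The case against.** The 95% has a printed source in the pilot's 95.8%, and the section also says that a high NPV is required, so 95% may be partly a target. The 126 follows correctly from it. Both points stand: the fault lies in the planning value, not in the calculation. But the paragraph presents the calculation as resting on the pilot data, and those data do not give 95% at 31% prevalence on either reading.

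A reader might infer from the pilot sensitivity and specificity that the expected NPV is 88.6% and that missed disease is more than double the planned 5%. The document does not support so firm a statement. It shows that the figures conflict, not which ones are misprinted. Reading B gives about 8%, although it in turn contradicts the stated 30% prevalence.

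A reader might also take the 91% as a sensitivity, pair it with the pilot specificity, and conclude that 209 should be 126 / 0.560 = 225. That depends on giving a label to a number in a visibly broken sentence, whose missing words may be an artefact of text extraction. Sensitivity 91% with specificity about 83% fits 209 and an NPV of about 95% equally well. Neither pairing is printed, so no error in the total is established.

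Finally, this is an estimation study in people attending for colonoscopy, and the Pilot work section itself says that accuracy must be established in the target population. That limits the consequence but does not reconcile the printed figures.

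**Conclusion.** The point holds as an internal contradiction in the pilot figures that carries through to the sample size justification. The printed sensitivity, specificity, PPV, NPV and prevalence cannot all be right; the gaps at 30% prevalence are about 15 points for PPV and 7 for NPV. At the planned 31% prevalence the pilot supports an NPV of roughly 88.6% to 92.1%, not 95%. With 126 test negatives the 99% half-width is then roughly ±7.3 to ±6.2 points, not ±5.

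This rests on three assumptions: normal-approximation intervals, sensitivity and specificity that carry over to the screening population, and one or the other group of pilot figures being correct. The pilot 2x2 table could move the values. The finding does not show that 126 is miscalculated, that 209 is wrong, or that the study must be enlarged.

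**What to change.** - **Pilot work:** check the printed figures against the pilot 2x2 table and correct whichever are wrong, including the prevalence if the PPV and NPV belong to a different denominator.
- **Sample size estimation:** restate the paragraph from one coherent set of sensitivity, specificity and prevalence. Give the NPV these imply at 31% and the half-width that 126 test negatives deliver. Until the table is checked, state this as roughly ±6.2 to ±7.3 points at 99% confidence.
- **If 95% is kept:** call it a target and give the sensitivity and specificity it assumes at 31% prevalence. Note that at specificity 77.1% it needs sensitivity of about 91%, above the pilot's 77.9%.
- **The total:** complete the sentence, label the 91%, and show how 209 follows from 126.

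The cost is a check of the pilot table and the rewording of two paragraphs. The stated NPV and precision become less favourable; no extra patients are needed.
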